# losses to follow-up and premature withdrawal from the trial

The reasons for which a subject may be withdrawn from the trial are as follows:

- Demand from the patient, withdrawal of consent;
- Clear aggravation;
- Occurrence of a serious or unpleasant adverse effect associated with the product tested;
- Poor compliance
- Occurrence of myeloproliferative syndrome;
- Initiation of thyroid hormone treatment during the trial (patients already on thyroid extracts treatment for more than 3 months may be included);
- Treatment with folic or folinic acid (other than the product studied) for more than two months during the trial.

The reasons for the treatment being stopped early or for premature withdrawal from the trial should be documented and reported clearly in the observation notebook, on the appropriate page. All cases of premature cessation of treatment or withdrawal will be analysed in terms of tolerance and efficacy, provided that it is possible to obtain the appropriate data.

The number of subjects lost to follow-up should be minimised and as much information as possible should be collected for these subjects (by postal or telephone contact, for example).

# data processing and statistics

All the variables will be subject to statistical analysis, but any adverse effects will also be analysed on a case-by-case basis.

## number of cases

The number of subjects required has been determined with nQuery Advisor® software. Calculations have been carried out for developmental quotient, based on previous data and the following assumptions for calculation of the number of subjects per group:

Two-tailed Student's t tests with equal numbers in the two groups

 risk 0.05

Mean improvement on placebo over one year 0.666 years

Mean improvement on folinic acid over one year 0.900 years

Standard deviation 0.4 years

Power (1-) 80%

Two-group t test (identical numbers of subjects each group); power (puissance); number of subjects per group

If we adopt a power of 80%, as is usual for phase II-III studies, we require 47 subjects per group (94 in total). We have therefore decided to recruit 50 subjects per group, giving 100 complete observations in total.

An intermediate statistical analysis will be carried out without decoding for the first 60 subjects, to check that the variances of the two groups are equal. The number of subjects required will be recalculated at this point. If the number of subjects must be changed, an amendment to the protocol will be required.

## data input, decoding and analysis

A double-input system will be used before decoding. Once the data have been cleaned in this way and the base has been corrected, the database will be frozen. Decoding will not take place until this has been achieved.

The analysis will concern the patients receiving the product and will include:

- An analysis of the study population for the principal descriptive variables: age, sex, selection criteria, maternal and paternal ages, term, birth weight, birth height, CC at birth, APGAR score and, at each consultation, height, weight, CC, examination, treatment, DA, DQ, CGI, parental opinion etc.,
- An analysis of clinical tolerance,
- An analysis of biological tolerance (blood formula, iron, ferritin, thyroid assessment) based on statistical methods (changes in biological features between C0 and Cf), analysing all data outside the normal range,
- An analysis of efficacy based on the variables defined above, with retrospective stratification for initial DQ.

## Tests used

Quantitative data will be analysed by Student's t tests (or ANOVA). For statistical analyses of laboratory test results, data may be adjusted before the analysis, according to JAMA norms [[[17]](#endnote-17)]. At the end of treatment, for quantitative data also available at the start of treatment (height, weight, CC, DA, biological test results), tests will be carried out to assess the change in the item considered under treatment (If-I0) rather than on the absolute value of the item after treatment (If). If the data are non-normally distributed and it is impossible to normalise them by an appropriate transformation, they will be analysed with the non-parametric Mann and Whitney U test.

For qualitative variables, Pearson's 2 test will be used for comparisons, with Fisher's exact test used if sample size is considered insufficient.

Statistical analysis will be carried out by the monitor from the CMJL, using PCSM® (Deltasoft) and SPSS® software. If necessary, assistance will be sought from a specialist organisation (SAS software).

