***Statistical methods*** Student's t tests (or Mann-Whitney U tests) for quantitative variables and 2 tests for qualitative variables. PCSM® (Deltasoft) and SPSS® software will be used, together with SAS if required.
Stratification will be carried out retrospectively, based on initial development quotient.

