### Randomisation

Prospective randomisation, based on the use of random number tables, will be applied. Randomisation will be carried out in blocks to prevent imbalance between the two groups. This randomisation will be carried out by an organisation independent of the Centre Médical Jérôme Lejeune.

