### Efficacy

Efficacy will be evaluated using several criteria.

The principal evaluation criterion will be the change in developmental age, the profile of which is known for patients with Down's syndrome [[[16]](#endnote-16)]:

Translation for the figure: Age mental = mental age; Age reel = real age.

Developmental age will be assessed by the revised Brunet-Lezine test administered before (DA0) and after (DAf) treatment: (DAf - DA0). The revised Brunet-Lezine test is widely recognised as a test for the evaluation of psychomotor development in infants. It has been validated and its metrological qualities (sensitivity, fidelity-homogeneity, dispersion and validity, including for Down's syndrome children) are well known. For further information about this test, please consult reference 13.

The other criteria for efficacy evaluation will be:

- CGI, as recorded by the doctor;
- A score for psychologist satisfaction, estimated on a VAS, evaluating the opinion of the psychologist on the subjective improvement of the child since the start of treatment.
- The response of the parents to the question "If possible, would you like to continue this treatment ?" The response will be scored as follows: in favour of continuing treatment/against continuing treatment/does not know or no opinion expressed.

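### The primary test on change in developmental age leaves age at entry unadjusted and uses baseline development inefficiently; a pre-specified ANCOVA would cost almost nothing

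*Protocol*

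**What the plan says.** - **Endpoint** (Protocol, Efficacy): "The principal evaluation criterion will be the change in developmental age", defined as DAf − DA0.
- **Test** (Protocol, Tests used): "Quantitative data will be analysed by Student's t tests (or ANOVA"), and for variables also measured at the start, DA among them, "tests will be carried out to assess the change in the item considered under treatment (If-I0) rather than on the absolute value". If the data cannot be normalised, "they will be analysed with the non-parametric Mann and Whitney U test". No covariate is named for either test.
- **Sample size** (Protocol, number of cases): based on the same unadjusted two-group t test.
- **Use of baseline** (Protocol, data input, decoding and analysis): "An analysis of efficacy based on the variables defined above, with retrospective stratification for initial DQ". The Protocol Summary agrees: "Stratification will be carried out retrospectively, based on initial development quotient". Neither place gives the cut-points, the number of strata or how they are combined. Neither says whether the strata belong to the primary test or form a separate subgroup look. Age, DA and DQ appear in the same section only as descriptive variables.
- **Allocation** (Protocol, Randomisation): "Randomisation will be carried out in blocks to prevent imbalance between the two groups". No stratification factor is named, so blocking balances numbers and not age or DQ.

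**The concern.** Developmental age is measured in children whose age at entry spans a four-fold range, about 6 to 24 months. The protocol itself treats baseline development as relevant, since it stratifies efficacy on initial DQ. If entry age or baseline development predicts the yearly gain, a t test on the change leaves that variation in the error term. DA0 enters only with a fixed coefficient of 1, and age enters at most indirectly, through DQ.

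Two things are at stake. The first is precision in a trial of 100 children. The second is protection against a chance imbalance that allocation does not control. In addition, strata without stated cut-points leave a further efficacy result of unclear status beside the main one.

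**Working it through.** **Inputs from the protocol (number of cases).** Gain on placebo 0.666 years, on folinic acid 0.900 years, so the difference is 0.234; SD 0.4; two-sided alpha 0.05; 80% power; 50 per group. That section calls the variable developmental quotient, but its figures are in years, so I read them as change in DA.

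**Assumed, because the documents do not give it.** r, the multiple correlation between the baseline covariates and DA gain.

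**Step 1: reproduce the plan.** Power is the probability that a noncentral t variable with 2n − 2 degrees of freedom and noncentrality 0.234 / (0.4 × √(2/n)) exceeds the two-sided 5% limit. At n = 47 power is 80.1%, so the stated 47 per group is confirmed. At n = 50, √(2/50) = 0.2, the noncentrality is 0.234 / 0.08 = 2.925, and power is 82.5%.

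**Step 2: adjustment compared with a plain t test.** Residual SD = 0.4 × √(1 − r²), with two degrees of freedom removed for two covariates.

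| r | Residual SD | Power at 50 per group | n per group for 80% |
|---|---|---|---|
| 0 | 0.400 | 82.5% | 47 |
| 0.3 | 0.382 | 85.9% | 43 |
| 0.5 | 0.346 | 91.7% | 36 |

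At r = 0, removing two or even three degrees of freedom leaves power at 82.5% to one decimal.

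**Step 3: adjustment compared with the planned DQ strata.** Suppose yearly gain equals DQ plus noise with total SD 0.4, so that r = SD(DQ)/0.4. Take DQ as normal with mean 0.666, ages uniform over 6 to 24 months, and DA = DQ × age. All of these are assumptions; the protocol gives neither a DQ formula nor a DQ distribution. Two equal strata capture 2/π = 0.64 of the DQ variance and three capture 0.79. A linear model in DA0 and age captures about 0.89 (simulation). Multiply r² by these shares to get R², then take the residual SD as 0.4 × √(1 − R²).

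| r (implied SD of DQ) | Two DQ strata | Three DQ strata | DA0 + age |
|---|---|---|---|
| 0.3 (0.12) | 84.7% | 85.2% | 85.5% |
| 0.5 (0.20) | 88.4% | 89.9% | 90.7% |

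The gain over the strata is 0.3 to 0.8 points at r = 0.3 and 0.8 to 2.3 points at r = 0.5, so roughly 0.5 to 2 points overall. Entering DQ itself as a continuous covariate would recover the full figures of step 2 under this mechanism.

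**Step 4: if gain depends on age itself.** Suppose gain falls by 0.4 years per year of age (illustrative, with no source in the documents). The SD of age is 1.5/√12 = 0.433 years, so the explained variance is (0.4 × 0.433)² = 0.030, and R² = 0.030/0.16 = 0.19. DQ strata recover essentially none of this, so power stays at 82.5%. DA0 plus age gives a residual SD of 0.361 and power of about 89.5%.

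**Step 5: chance imbalance.** With uniform ages the SD is 18/√12 = 5.2 months. The SE of the between-arm difference in mean age is 5.2 × 0.2 = 1.04 months, so the 95% range is about ±2.0 months. If age correlates 0.3 to 0.5 with gain, an imbalance at the edge of that range moves the estimate by r × 0.4 × 1.96 × 0.2, which is about 0.05 to 0.08 years, against a target of 0.234.

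**The case against.** The strongest reply is that nothing here is an error. A two-sample t test on change is unbiased under randomisation, matches the endpoint and the sample-size calculation, and has a standard error that already allows for chance imbalance. All of that stands. A reader might infer that the primary test is invalid or the sample size wrong; neither follows, and 47 per group reproduces exactly.

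The second reply is that baseline is not ignored. DA0 is subtracted, efficacy is to be analysed "with retrospective stratification for initial DQ", and ANOVA is allowed. This stands in part. If the strata belong to the main analysis and gain follows DQ, most of the available precision is already recovered (step 3). Power figures of 92% and above should therefore not be read as the gain over the actual plan. They also need a wide DQ spread: under the step 3 mechanism, r = 0.5 means a two-SD range of about 0.27 to 1.07. What does not stand is the idea that age is covered. It enters at most through DQ, and DQ strata do not pick up a direct age effect.

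Third, a reader might infer that retrospective strata mean cut-points picked after unblinding. The documents do not say so. Initial DQ is a pre-treatment variable, the database is frozen before decoding, and the word may simply distinguish post-stratification from stratified randomisation. What remains is that the protocol does not commit to fixing the cut-points by then.

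Finally, covariates and cut-points are often left to an analysis plan, and one may exist. The point survives because the protocol itself makes the choice of test and of change score.

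**Conclusion.** The point holds as an inexpensive improvement, not as a defect of validity. The protocol fixes an unadjusted comparison of DA change and uses baseline otherwise only through loosely specified DQ strata, while DA0, age and DQ are available for every child assessed at entry.

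The size is uncertain. Compared with a plain t test, adjustment is worth about 3 points of power at r = 0.3 and 9 at r = 0.5. Compared with a DQ-stratified analysis it is worth about 0.5 to 2 points if gain follows DQ, and about 7 points in the illustrative case where gain depends on age. Both r and the mechanism are assumptions, so the benefit runs from nil to substantial. The cost is negligible throughout that range.

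**What to change.** Before decoding, amend the Tests used section and the efficacy item under data input, decoding and analysis:

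- **Primary analysis:** ANCOVA of 12-month DA (or of the change) on treatment, with DA0 and age at entry as continuous covariates. Initial DQ may be added as a continuous covariate. Report the adjusted difference with its 95% CI.
- **Sensitivity analysis:** the unadjusted t test on DAf − DA0.
- **Initial DQ as a subgroup factor:** a single treatment-by-baseline-DQ interaction labelled exploratory. Alternatively, keep the strata, with cut-points, number of classes and method of combination written down before decoding.

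This changes wording only. No new data are needed, because the Brunet-Lezine test is done at the first consultation and age and DQ are already among the listed variables. The statistical price is two to three degrees of freedom out of 98. The sample size can stay as planned.

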# ethical issues

This trial will be carried out in accordance with:

- The recommendations of the Helsinki Declaration, provided in the appendix
- Good clinical practice, as defined by the International Conference on Harmonisation (CHPH/ICH/135/95, adopted on 17/07/1996)
- The Huriet Law (dating from 20/12/1988), as amended by the laws of 23/01/1990 and 25/07/1994 and their decrees of application
- The law of 01/07/1994 relating to the processing of nominative data collected for health research, amending the *Loi Informatique et Libertés* (Computing and Liberty Law) dating from 06/07/1978.

## Good clinical practice

This study will be carried out according to the standardised operating procedures (SOP) of the Centre Médical Jérôme Lejeune. These procedures are available as a manual.

## ethics committee, Irb

The Co-ordinator will submit this protocol to the IRB of Saint-Germain en Laye Hospital, by recorded post (with notification of delivery), providing the information required by article R.2029 of the French Public Health Code.

All modifications to the protocol must be submitted to this IRB for approval in cases of substantial modification or for notification in cases of minor modification, and will be communicated to the AFSSaPS if necessary.

## Qualifications

The medical director of the centre is [name], Professor of Genetics and Member of the Academy of Medicine. She is clearly competent to co-ordinate this trial. The doctors of the centre have considerable experience in the field of mental disability and have attended additional, appropriate training. They have also already worked as investigators in clinical drug trials. The psychologists routinely carry out evaluations of the patients followed at the CMJL. The knowledge and experience of the personnel involved in this trial are therefore consistent with the research proposed.

The *curriculum vitae* of the participants in this trial are supplied in the appendix.

## adequacy of the research site

The Centre Médical Jérôme Lejeune has accreditation from the French Ministry of Health as a referral centre for the follow-up of diseases of chromosomal origin affecting intelligence. Down's syndrome patients account for 75% of the patients followed at the CMJL. This centre has accreditation for biomedical research without direct individual benefit, covered by authorisation number 10435S, issued on April 8th 1999.

The facilities of the CMJL include an infirmary with an emergency care kit specially designed for clinical trials. This centre is located within Notre Dame de Bon Secours Hospital, which has an emergency department. If required, the nearest available intensive care unit is that run by [name] at Saint Joseph Hospital, 800 metres away. This site is therefore entirely appropriate for this clinical study, particularly given that tolerance to folinic acid is considered to be excellent: according to the Vidal guide (see appendix), folinic acid is non-toxic; no overdose has ever been observed, including during the administration of very high doses. Indeed, once the amount required by the body has been used, the excess is eliminated.

## Information of the patients and informed consent

The legal representative (parent or guardian) of the child will be informed of the aims of the research, its duration, the methods used, the advantages and possible constraints and risks. This information will be provided by the investigator, in the form of an information sheet given to the patient's legal representative. This information sheet is provided in the appendix.

Written informed consent will be obtained from the subject's legal representative. The text of the consent form is provided in the appendix. The presence of a signed consent form will be checked during monitoring of the trial, whilst respecting medical secrecy. Consent forms will be stored in sealed envelopes at the CMJL and will be archived at the end of the study.

## Anonymity

All individuals involved in the running of this trial will be required to respect professional secrecy. In addition, the anonymity of the patients will be maintained. In France, these requirements are laid down in article R.5120 of the Public Health Code.

Finally, data processing will be carried out in accordance with the laws in force, including the Law "*Informatique et Libertés*" dating from January 6th 1978 and its decrees of application.

# practical considerations

## duration of the trial

The total duration of the inclusion period will be 1.5 years.

## monitoring

Regular telephone contact (at least every two months) will be established, in addition to consultations with investigators and/or the monitor and/or the nurse at the CMJL. For data checking, direct access to the source data for the patients (medical files) will be required and will be supplied by the investigator to allow the monitor to make comparisons with the data collected in the observation notebook.

## Audit

Audits of the trial and of files relating to the trial will be carried out before the trial, at the start of the trial and after the trial, before decoding, by PRA International-ARCAM ([name]). Other audits may also be carried out.

## recording and archiving of data

Data will be recorded legibly, with a black ballpoint pen, in the observation notebook. The missing data will be clearly indicated as ND (not determined) or NA (not applicable).

Corrections made before the separation of duplicate entries will be made by crossing out the incorrect data such that they remain legible. The correction will then be written alongside the original data, signed and initialled. Errors detected after the separation of duplicate entries will be corrected using dedicated sheets in which the initial data and the corrected data will be noted, together with the date and the investigator's signature.

The investigator and the sponsor must keep the essential documents relating to this trial (source data, originals of the informed consent forms) for at least two years after the end of the last authorisation for market release obtained in an ICH region and until there are no more demands for market release pending or envisaged in an ICH region.

## final report, publication, confidentiality

This trial may not be the subject of any written or oral communication (publication, communication) without the agreement of the CMJL (article R.5120 of the French Public Health Code).

In case of publication, the order of the authors will be determined amicably, on principle as follows: the investigating doctors, the monitor, the psychologists and the co-ordinator. Laboratoires Thérabel-Lucien Pharma will be acknowledged at the end of the article.

# administrative procedures

These procedures will respect the legislation in force in France.

## insurance

The guarantees of the insurance contract covering civil responsibility taken out by the CMJL will apply, in accordance with the Law of December 20th 1998, particularly as concerns article L.209-7 of the Public Health Code (civil responsibility contract for the sponsors of biomedical research taken out with an insurance company specialising in health risks: SM Biomédic, [name]).

## DEclaration of intent to the AFSSaPS

A letter of intent will be sent to the AFSSaPS (*Agence Française de Sécurité Sanitaire pour les Produits de Santé*) by recorded post (with notification of delivery), by the sponsor, and will include the details required by article  R.2032 of the French Public Health Code.

## Information of the directors of health establishments

A letter of declaration will be sent by the monitor to the Director of the Centre Médical Jérôme Lejeune, including the details required by article R.5124 of the French Public Health Code.

## Information of pharmacists of health establishment

NA.

## financial conventions

No financial conventions have been signed concerning this trial.

# DOCUMENTS supplied in the appendix

-  VIDAL guide entry concerning Folinoral®

- Helsinki Declaration

- Information sheet (Art. L.209-9 of the French Public Health Code) and informed consent form (Art. L.209-9 of the Public Health Code)

- Example of completed revised Brunet-Lezine test

- *Curriculum vitae* of the study participants

- Presentation of the CMJL

